# Randomised feasibility trial and embedded qualitative process evaluation of a new intervention to facilitate the involvement of older patients with multimorbidity in decision-making about their healthcare during general practice consultations: the VOLITION study protocol

**DOI:** 10.1186/s40814-020-00699-7

**Published:** 2020-10-26

**Keywords:** Primary care, Elderly, Older people, Multimorbidity, Shared decision-making, Patient involvement

## Abstract

**Background:**

The number of older people with multiple health problems is increasing worldwide. This creates a strain on clinicians and the health service when delivering clinical care to this patient group, who themselves carry a large treatment burden. Despite shared decision-making being acknowledged by healthcare organisations as a priority feature of clinical care, older patients with multimorbidity are less often involved in decision-making when compared with younger patients, with some evidence suggesting associated health inequalities. Interventions aimed at facilitating shared decision-making between doctors and patients are outdated in their assessments of today’s older patient population who need support in prioritising complex care needs in order to maximise quality of life and day-to-day function.

**Aims:**

To undertake feasibility testing of an intervention (‘VOLITION’) aimed at facilitating the involvement of older patients with more than one long-term health problem in shared decision-making about their healthcare during GP consultations.To inform the design of a fully powered trial to assess intervention effectiveness.

**Methods:**

This study is a cluster randomised controlled feasibility trial with qualitative process evaluation interviews. Participants are patients, aged 65 years and above with more than one long-term health problem (multimorbidity), and the GPs that they consult with. This study aims to recruit 6 GP practices, 18 GPs and 180 patients. The intervention comprises two components: (i) a half-day training workshop for GPs in shared decision-making; and (ii) a leaflet for patients that facilitate their engagement with shared decision-making. Intervention implementation will take 2 weeks (to complete delivery of both patient and GP components), and follow-up duration will be 12 weeks (from index consultation and commencement of data collection to final case note review and process evaluation interview). The trial will run from 01/01/20 to 31/01/21; 1 year 31 days.

**Discussion:**

Shared decision-making for older people with multimorbidity in general practice is under-researched. Emerging clinical guidelines advise a patient-centred approach, to reduce treatment burden and focus on quality of life alongside disease control. The systematic development, testing and evaluation of an intervention is warranted and timely. This study will test the feasibility of implementing a new intervention in UK general practice for future evaluation as a part of routine care.

**Trial registration:**

CLINICAL TRIALS.GOV registration number NCT03786315, registered 24/12/18

## Background

It is estimated that by 2032, there will be over 13.5 million patients in the UK aged 65 years and over, an increase of 50% when compared with 9 million in 2012 [36]. The prevalence of multimorbidity (more than one long-term health condition) increases with age [1]; 58% in people over 60 years compared with 14% in those under 40 years [30, 42, 43]. In developed countries, the prevalence of multimorbidity is also higher in females, among those with lower socioeconomic status (SES) and in minority ethnic groups [11, 45]. In those with lower SES, it is more common for mental and physical illness to co-exist. In addition, patients’ experiences of multimorbidity are affected by psychosocial and behavioural factors and larger health inequalities have been observed in vulnerable groups [39].

Consequences of ageing with multimorbidity include functional decline with poor quality of life and high healthcare costs [1, 26, 32]. The Department of Health [15] reported that older patients (those aged 65 and above) consult increasingly frequently (12–14 times/year in 2008/2009 vs. 6–7 times in 1995). Healthcare practitioners are often ‘medicalising’ the care of older people, diagnosing and treating each condition separately with new medication for example, and there are increasing rates of polypharmacy and new diagnoses [16].

There is evidence that involvement in healthcare decision-making is valued by older patients with multimorbidity [4, 9]. It is a means of effectively sharing the burden of treatment and enabling a holistic approach to clinical care [48]. Despite older patients typically expressing high levels of satisfaction with the care that they receive [7], they have been shown to be less frequently involved in decision-making when compared with younger, healthier patients [49], and there is a lack of recent evidence in this area. Therefore, whilst this patient group are often in receipt of ‘good-quality care’, there are concerns that this care is not currently meeting the complex needs of older patients with multimorbidity [48]. In addition, there is some evidence of an association between a lack of involvement and health inequalities for this patient group, for example, reduced rates of referral for postmenopausal bleeding and for hip pain [17, 28, 46].

Interventions aimed at facilitating shared decision-making between doctors and patients have previously focused on condition-specific clinical decisions. These interventions are therefore outdated in their assessments of today’s older patient population who often have complex needs as a result of multimorbidity [23, 38]. Recent literature suggests that new interventions are required in order to address older patients’ fundamental needs and life-goals, to support these patients in prioritising treatment options that maximise their quality of life and day-to-day function [48].

National Institute for Health and Care Excellence (NICE) guidance highlights the importance of delivering good-quality clinical care that takes account of multimorbidity [34]. The World Health Organisation [51] and UK health policy [14, 35] have identified shared decision-making as a priority feature of good-quality clinical care. Shared decision-making is a component of patient-centred care and is associated with patient adherence with treatment advice, satisfaction with healthcare and trust in the doctor [13, 20, 25, 37]. Policy makers require further evidence-based guidance regarding how to direct funding towards good quality clinical care for older patients with multimorbidity when consulting in general practice [5, 34].

An effective intervention in this area has the potential to address health inequalities through the facilitation of effective, personalised care that addresses patients’ fundamental needs holistically. The intervention has the potential to achieve positive outcomes for both patients and practitioners, along with reductions in primary healthcare costs for the National Health Service. This study aims (a) to feasibility test the delivery and evaluation of the intervention ‘VOLITION’, and (b) to carry out process evaluation of intervention and study procedures.

## Objectives

### Feasibility objectives

Feasibility objectives will assess:
Capability to recruit and the resulting characteristics of the sampleData collection processesPotential outcome measuresResource and capacity for study management and intervention implementationResponses to the intervention by participants (tentative, preliminary evaluation)

### Process evaluation objectives

Process evaluation objectives will assess:
Acceptability of the intervention to patients and GPsAcceptability of study procedures to practices and participants

The feasibility and process evaluation findings will together inform strategies to address any challenges in trial and intervention delivery. Findings will inform the design of a future fully powered, large-scale, randomised controlled trial to formally evaluate the effectiveness of the intervention.

## Methods

### Trial design

This study is a cluster randomised controlled feasibility trial with embedded qualitative process evaluation.

Figure 1 shows the schedule of enrolment, interventions and assessments as a SPIRIT figure.

**Fig. 1 Fig1:**
[figure not shown]
Testing VOLITION: schedule of enrolment, interventions and assessments

### Sampling

Six GP practices will be recruited from rural Devon and from each of the cities of Exeter and Plymouth, UK. A minimum practice size of 3000 patients will ensure sufficient numbers of eligible participants. (It is anticipated that there will be approximately 800 older patients with multimorbidity in an average 8000 patient practice [1]). Table 1 shows the participant inclusion and exclusion criteria. An average of three (total = 18 GPs), and at least 2, GPs per practice will be recruited. Patients aged 65 and above with known multimorbidity, defined as the presence of two or more long-term conditions (as specified in Table 1), will be approached.

**Table 1 Tab1:** Participant inclusion and exclusion criteria

Participant type	Inclusion criteria	Exclusion criteria
GPs	Only permanent GPs (partners and salaried) to avoid loss to follow-up.	Locum (sessional) GPs Trainee GPs (GPs will not be excluded based on less than full time working)
Patients	Patients aged 65 and above with known multimorbidity The condition should be one of^a^: angina or long-term heart problem; arthritis or long-term joint problem; asthma or long-term chest problem; blindness or severe visual impairment; cancer in the last five years; deafness or severe hearing impairment; diabetes; epilepsy; high blood pressure; kidney or liver disease; long-term back problem; long-term mental health problem; long-term neurological problem.	Temporary residents and vulnerable patients e.g. those recently bereaved, those with severe mental illness, severe cognitive impairment, end stage disease, communication difficulties e.g. physical impairment caused by a stroke as opposed to language barriers, a learning disability, or those unable to complete questionnaires or interviews for any other reason. (A minimum time for a condition to be ‘long-term’ will not be specified)

^a^This list was adapted from the English National General Practice Patient Survey [10]. Where dyads of conditions occur within the same organ system, e.g. anxiety and depression, these will only be counted once e.g. mental health problem

Patient participants will be identified using an automated practice database search strategy designed by the research team. The practice administrative team will use this ‘flag’ to identify ten consecutive potential participants with pre-booked consultations with each of the three recruited GPs. Random sampling of participants is not required as the clinical presentations, and therefore the nature of the decision-making between consecutive consultations, is expected to be random. A total of 180 (minimum 120) potential patients will be identified across 6 practices, with the aim of recruiting at least half.

The sample size is sufficient to compare between-group differences in quantitative feasibility objectives such as recruitment rates and data collection procedures including the completeness of participant questionnaires. This sample size also allows the estimation of standard deviations for the clinical outcome measures being tested. In addition, it is sufficient to obtain a purposively selected sub-sample of participants for process evaluation interviews, to achieve the qualitative feasibility objectives.

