### Recruitment procedures

Non-compliance with the intervention will be taken into account at patient, GP or practice level by over-recruiting. Practices will receive email and phone correspondence inviting their participation. Practice recruitment will be dependent on an expression of interest from at least two of their GPs. Practices will be incentivised through payment for local coordination and set-up. GPs will receive a certificate for the training course (Williamson et al. 2007).

For each recruited GP, ten potential patient participants with pre-booked appointments will be screened by GPs, and if eligible, contacted by post ahead of their appointment. They will receive a cover letter, participant information sheet and example consent form. On their arrival in the practice waiting room, the receptionist will provide the patient with a pre-consultation questionnaire.

Patients who do not wish to participate will indicate this with a tick box on the pre-consultation questionnaire. Practices will keep an anonymised log of patients who declined to participate. A tick box on the post-consultation questionnaire will enable patients to opt out of process evaluation interviews and/or from having their case notes reviewed.

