#### Evaluation of data collection

Table 3 outlines the feasibility measures to be assessed regarding the collection of outcome data.

**Table 3 Tab3:** Evaluation of data collection procedures

Type of data collection (patient-, GP- or researcher-facing)	Components to be reviewed	Methods of analysis	Potential resultant amendments ahead of a definitive, larger trial
Patient-facing (questionnaires)		All patient-facing data collection forms have been reviewed for their suitability by Patient and Public Involvement (PPI) group	PPI members advised on the wording and format of questionnaires. PPI will provide a lay perspective on interpretation of feasibility findings.
	The feasibility of distribution and collection of patient questionnaires by receptionists.	Researcher’s field notes and follow-up correspondence with practices. Process evaluation interviews with patients.	Consideration of distribution by another means e.g. in the post (or email) prior to consultation.
	The appropriateness of collecting demographic data by patient self-report on pre-consultation questionnaires, as opposed to through the medical record.	Review of completeness of relevant items on patient questionnaires. Process evaluation interviews to discuss potential reasons for missing data. Correspondence with practices regarding practicalities of accessing patient demographic data with consent.	Consideration of accessing patient baseline data through practice records.
	Whether patient participants require assistance, encouragement or supervision to complete either of the questionnaires.	Researcher’s field notes and process evaluation interviews.	The provision of assistance to patients when completing questionnaires, e.g. providing staff to assist them or allowing more time pre- or post-consultation to allow the patient to seek help from a third party.
	Issues regarding time taken for questionnaire completion, any difficulties with comprehension of questionnaire items, numbers of questionnaires returned and reasons for missing data	Relevant quantitative data will be reported descriptively. Issues will be explored qualitatively with patients during process evaluation.	Time taken for completion may inform decisions surrounding when and how to distribute questionnaires. Issues regarding comprehension of specific items may lead to rewording with the assistance of the PPI group.

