### Process evaluation using qualitative methods

A qualitative interview study, embedded within the feasibility trial with data integration.

Fifteen patients from intervention practices will be sampled and twice this number will be approached. Patients will be selected purposively and iteratively, using questionnaire data to ensure heterogeneity by age, sociodemographic characteristics, health status and preference for shared decision-making (Coyne 2008). Patients will be contacted by telephone to arrange an interview. All GPs in the intervention group will be invited by email. The sample size will be reviewed when assessing thematic saturation [22].

Following receipt of post-consultation participant questionnaires, semi-structured interviews aided by a topic guide will be digitally audio recorded, transcribed and supported by field notes. Participants will be encouraged to discuss their own ideas in order to collect fresh data without the influence of the researcher (Britten et al. 1995). Data will be collected regarding:

Participant experiences of the intervention
Acceptability of the interventionInfluences for intervention implementation and integration into normal practiceWhether participants perceive the intervention to be effective

Participant experiences of the study
How study participation was experiencedWhether study participation induced behaviour change not prescribed by the intervention

Audio recordings will be coded using Nvivo computer software (Mills, Bonner and Francis 2006). Data analysis will take a sequential-explanatory approach, combining both deductive and inductive methods to investigate whether the theory developed earlier in the project holds, but also being open to new data and emerging themes [31]. The concept of inductive thematic saturation [21] (Maykut and Morehouse 1994) will be applied and negative cases will be actively sought [44]. The consistency with which the coding is applied will be assessed on a fifth of the data [29]. Analytic meetings will be held with the research team to discuss validity. Data will be interpreted within the context of possible cause–effect pathways of the intervention.

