### Criteria for progression to a future definitive randomised controlled trial of the intervention

Study processes are designed to be iterative, formative and adaptive [6]. However, there are certain criteria on which progression to a future, larger trial of intervention effectiveness is dependent. These are:
Recruitment
> 80% of general practices approached (i.e. 5/6)> 60% of GPs approached per practice (i.e. 2/3)> 50% of patients approached per practice (i.e. 20/30)Collection of outcomes
> 60% of patient-reported outcomes (questionnaire response rate)> 70% of patient questionnaire respondents providing written consent to case-note review> 70% of video recordings useable for observer ratings

Loss to follow up is expected to be minimal and is therefore not included as a ‘stopping criteria’.

The Chief Investigator, the Trial Steering Committee and the sponsor have the authority to stop or advise modifications to the feasibility trial.

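### Table 1 excludes trial-wide anyone unable to be interviewed, though only 15 patients are to be interviewed, and its questionnaire limb makes the 60% response criterion conditional on GP screening

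*Protocol article*

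**What the plan says.** The patient exclusions in Table 1 (Sampling) list several vulnerable groups and close with "or those unable to complete questionnaires or interviews for any other reason". The clause has no threshold and does not say whether completing a form with help counts as being able.

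Under Recruitment procedures GPs apply the criteria before contact: "ten potential patient participants with pre-booked appointments will be screened by GPs, and if eligible, contacted by post ahead of their appointment". A tick box later lets patients opt out of interviews.

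The qualifying conditions in the same table include "blindness or severe visual impairment; cancer in the last five years; deafness or severe hearing impairment". The exclusion just before the catch-all covers "communication difficulties e.g. physical impairment caused by a stroke as opposed to language barriers".

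Table 3 (Evaluation of data collection) makes this a question to be studied: "Whether patient participants require assistance, encouragement or supervision to complete either of the questionnaires". The progression criteria require more than "60% of patient-reported outcomes (questionnaire response rate" to be met.

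On interviews, the process evaluation section says: "Fifteen patients from intervention practices will be sampled and twice this number will be approached". They are arranged by telephone and audio-recorded.

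The analysis section on recruitment plans an anonymised profile of ineligible patients and will consider adaptations so that they could take part later. Strengths and limitations adds that including vulnerable patients in a future trial, with carers' involvement, will be considered.

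**The concern.** There are two separate problems in one clause.

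**Interview limb.** Ability to be interviewed is a condition of entry for every patient in both arms, yet interviews are a small, optional sub-study in one arm. A patient may refuse an interview and stay in the trial, but one considered unable to give an interview is kept out. Someone with severe hearing impairment may complete both questionnaires, be recorded in the consultation and have notes reviewed, and still be excluded because a telephone-arranged, audio-recorded interview looks impractical.

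**Questionnaire limb.** The study wants to learn whether older patients with multimorbidity need help with the forms. If GPs read the clause as unable to complete alone, the patients who would show that need are gone before approach. The response rate used for progression then describes a group already screened for ability to respond.

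At stake are the usefulness of the assistance finding, the interpretation of one progression criterion, and unnecessary loss of eligible patients.

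**Working it through.** **Planned numbers.** 6 practices × 3 GPs × 10 patients = 180, and 6 × 2 × 10 = 120 as the minimum. Both match the Sampling section. The same section aims to recruit at least half, so 90 of 180.

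**Interview limb (document figures only).** Table 4 lists interviews with 15 patients, all from intervention practices.
- With 180 patients (90 per arm): no control patient and 90 − 15 = 75 intervention patients are without an interview, so 90 + 75 = 165 of 180 = 91.7% are not interviewed.
- With 90 recruited: 90 − 15 = 75, so 75 of 90 = 83.3% are not interviewed.

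None of the patient outcomes in Table 4 (observer rating of the video, patient and GP questionnaires, case-note items) needs an interview. The limb therefore has no bearing on outcome measurement, and this result needs no assumption.

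**Questionnaire limb (illustration with assumed inputs).** Let r be the response rate over all flagged patients, x the share screened out as unable, and q the response rate the screened-out patients would have had. Response among the remainder is

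(r − xq) / (1 − x),

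and it reaches 60% when x = (0.60 − r) / (0.60 − q). The article gives none of r, x or q, so a range is shown.

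| r | x needed, q = 0 | x needed, q = 0.2 |
|---|---|---|
| 55% | 0.05/0.60 = 8.3% | 0.05/0.40 = 12.5% |
| 50% | 0.10/0.60 = 16.7% | 0.10/0.40 = 25% |
| 45% | 0.15/0.60 = 25% | 0.15/0.40 = 37.5% |

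Put the other way, with q = 0, a 60% rate after screening corresponds to 0.60 × (1 − x) of all flagged patients: 57%, 54%, 48% and 42% when x is 5%, 10%, 20% and 30%.

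**Chance of exceeding 60%.** Take r = 55%, q = 0, 180 flagged patients and independent binomial responses (clustering ignored):

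| x | Patients left | Needed for >60% | Response rate among them | Chance of passing |
|---|---|---|---|---|
| 0% | 180 | 109 | 55.0% | 8% |
| 5% | 171 | 103 | 57.9% | 30% |
| 10% | 162 | 98 | 61.1% | 60% |
| 15% | 153 | 92 | 64.7% | 90% |
| 20% | 144 | 87 | 68.8% | 99% |

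The direction is certain whenever q is below r. The effect on the decision matters only when r lies somewhat below 60%. With r = 70% the criterion is met with or without screening. With r = 40%, x = 10% and q = 0 the rate is 0.40/0.90 = 44.4%, which fails either way.

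**The case against.** **Excluding patients who cannot provide the patient-reported outcomes is common.** If the definitive trial keeps the same eligibility, response among eligible patients is the relevant rate. This stands, and it is why deleting the whole questionnaire limb would be a preference rather than a correction. It has less force here because the article itself contemplates widening eligibility.

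**Inability is not non-response.** Patients who decline, do not attend or leave items blank remain and can still make the criterion fail. Patients who need help are not necessarily unable. Both points stand, so the concern about the questionnaire limb depends on how GPs read it.

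**The filter will be visible.** A profile of ineligible patients and a review of exclusions are planned. This is real mitigation, but neither enters the progression criterion, and a profile cannot show whether those patients could have managed with help.

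**A condensed article need not define every term or denominator.** Accepted; no missing definition is counted as an error. The point is the criterion as written and the order of screening and counting.

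A reader might also infer three stronger things:
- *That the exclusion contradicts the list of conditions.* It does not. The list defines multimorbidity, while the exclusion concerns ability to provide data, and many patients with sensory impairment can complete a form. Language barriers have just been set apart in the table, so the natural reading is that the catch-all does not bring them back. This is tension and ambiguity only.
- *That progression can be secured by pre-selection.* This is possible in principle, but the screened-out share is unknown and nothing shows it would be large enough.
- *That GPs will apply the clause differently by arm because only one arm has interviews.* Table 1 is the same for both arms, nothing indicates different application, and differential recruitment is already to be examined.

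**Conclusion.** The point holds in a limited form. The interview limb is unnecessary as a trial-wide exclusion. It conditions entry on something irrelevant to outcome measurement for 83% to 92% of patients, depending on whether 90 or 180 take part, and it can remove people able to supply every outcome.

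The questionnaire limb is a weaker problem. If it is applied to patients who could complete with help, it works against the Table 3 question and makes the response criterion conditional on GP screening. Its size in this trial cannot be derived from the article. The calculations show only that, if true response over all flagged patients were just under 60%, screening out a modest share of non-responders could change the result. They rest on assumed rates, independence and, for the pass probabilities, no response at all among those screened out. The article does not support saying that the progression decision is compromised.

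**What to change.** 1. Remove the interview condition from trial eligibility and apply it only when choosing interviewees.
2. Restrict the questionnaire limb to patients unable to complete the forms even with a companion's help, and record assisted completion as such. State that sensory impairment or a language barrier alone does not exclude.
3. Count GP exclusions on this ground by arm, as part of the planned data on ineligible patients.
4. Report the questionnaire response rate for the progression criterion in two ways: among approached patients and over all flagged patients.

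This takes an edit to Table 1, one extra item in the screening log and one extra line in the report. The price is a somewhat lower reported response rate and some assisted or missing questionnaire data, and assisted answers may need to be looked at separately. Relying on companions avoids a call on the study's limited staff, although patients without one gain nothing from the change.
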